## Figures and Tables

**Figure 1 brainsci-15-00905-f001:**
[figure not shown]
Experimental framework: (**a**) Spectral characteristics of stimuli showing both spectrogram and pitch contour, (**b**) Schematic representation of the experimental apparatus, (**c**) Experiment workflow.

**Figure 2 brainsci-15-00905-f002:**
[figure not shown]
t-PCA pipeline for ERP data in the multi-feature oddball paradigm. (**A**) Data Matrix Setup. The matrix is labeled by Conditions × Time Points × Electrodes, representing trials collected across different stimulus types. (**B**) Covariance Matrix. Covariance matrix is essentially a mathematical tool that helps capture how the data varies over time and across different participants and conditions. (**C**) Principal component analysis. After we obtain the covariance matrix, the next step for t-PCA is to perform eigenvalue decomposition of the covariance matrix to extract the Principal Components from it. These principal components can be seen as new variables extracted from the original EEG signal, which reflect the change pattern of the maximum variance in the data. (**D**) Rotation. The principal components are adjusted using rotation techniques, such as Promax rotation, to improve interpretation. The purpose of the rotation is to make the interpretation between the individual principal components clearer and allow them to have correlations that are more in line with the actual electrical activity of the brain. (**E**) Component identification. By rotating the components, we can begin to identify the individual ERP components that make sense, such as eMMN, lMMN, and P3a. (**F**) Back-Projection and Reconstructed ERP. Components being projected back to ERP space. We multiply the loading matrix of each principal component with the factor scores under each condition to obtain the reconstructed waveform. The reconstructed waveforms contain the specific variation structure of each principal component in the ERP signal, and these waveforms can be interpreted in µV units, like traditional ERP waveforms. (**G**) Amplitude Extraction and Statistical Comparison. This final panel shows mean amplitude extraction from the reconstructed ERP data and reflects statistical testing (e.g., *t*-tests, ANOVA) to assess group differences or condition effects.

**Figure 3 brainsci-15-00905-f003:**
[figure not shown]
Workflow of RSA applied to ERP data from a multi-feature oddball paradigm.

**Table 1 brainsci-15-00905-t001:** Tentative Predictions for the Seven Stimulus Conditions (Based on EPF/WCC/NCH) Condition.

	Processing Type	Prediction in ASD	EPF + NCH Account	WCC + NCH Account
Consonant only	Local	↑ or = MMN amplitude ↓ or = MMN latency	Enhanced perception of phonetic detail	Intact
Vowel only	Local	↑ or = MMN amplitude ↓ or = MMN latency	Enhanced formant processing	Intact
Tone only	Global	↓ MMN amplitude ↑ MMN latency	Reduced prosodic integration	Impaired due to global integration load
C + V	Mixed/Global	↓ MMN amplitude ↑ MMN latency	Disruption due to multiple feature load	Integration weakness
V + T	Global	↓↓ MMN amplitude ↑↑ MMN latency	Disrupted holistic processing	Poor feature binding
C + T	Global	↓↓ MMN amplitude ↑↑ MMN latency	Disrupted holistic processing	Failure to form unified percept
C + V + T	Global	↓↓↓ MMN amplitude ↑↑↑ MMN latency	Collapsed integration under complexity	Strongest integration failure

Note: ↑ represents significant increase. ↓ represents significant decrease. = represents similar results when comparing MMN responses in ASD group with those in the TD group. Double/Triple arrows indicate magnitude increment/decrement.

**Table 2 brainsci-15-00905-t002:** Specific Predictions Based on MMN Literature-Based Predictions for Each Stimulus Condition.

Condition	MMN Amplitude in ASD	Latency in ASD	Reduced Left-Hemispheric MMN Dominance
Consonant only	↓	↑	Predicted—based on broader speech processing literature
Vowel only	= or ↓	↑	Predicted—but may be less pronounced than for consonants
Tone only	↓	= or ↑	Predicted—particularly for lexical tones
C + V	↓↓	↑↑	Predicted—likely pronounced
V + T	↓↓	↑↑	Predicted—key for tonal languages
C + T	↓↓	↑↑	Predicted—reflects integration challenge
C + V + T	↓↓↓	↑↑↑	Predicted—most pronounced reduction expected

Note: ↑ represents significant increase. ↓ represents significant decrease. = represents similar results when comparing MMN responses in ASD group with those in the TD group. Double/Triple arrows indicate magnitude increment/decrement.

**Table 3 brainsci-15-00905-t003:** Phonological Stimuli: Standard vs. Deviant Feature Variations.

Stimulus Type	Stimulus	Feature(s) Changed
Standard	/ba1/	None
Deviant 1	/ba4/	Tone change
Deviant 2	/bu1/	Vowel change
Deviant 3	/da1/	Consonant change
Deviant 4	/bu4/	Tone + Vowel Change
Deviant 5	/da4/	Tone + Consonant Change
Deviant 6	/du1/	Vowel + Consonant Change
Deviant 7	/du4/	Tone + Vowel + Consonant Change

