## 2. Materials and Methods

### 2.1. Participants

#### 2.1.1. Sample Size Justification and Ethics

The sample size for this study was determined using G*Power (version 3.1) [67]. A priori power analysis was conducted using an MANOVA: Repeated measures, within-between interaction framework as the study compares two groups (ASD vs. TD) with multiple MMN measures. Assuming a relatively large effect size (Cohen’s f = 0.25), the analysis indicated that a total sample size of at least 52 participants (approximately 26 per group) would be required to achieve a power of 0.80 at a significance level of α = 0.05.

This study will be conducted in accordance with the ethical guidelines and approved by the Human Research Ethics Committee for Non-Clinical Faculties at South China Normal University. Written informed consent is obtained from the legal guardians of all participating minors, and assent is secured from the children themselves. Participants are recruited voluntarily through collaboration with the Guangzhou Kangna School and Guangzhou Yongxing School, with explicit inclusion/exclusion criteria to ensure suitability. Risks are considered minimal, as the EEG procedure poses no physical or psychological harm, and participants are free to withdraw at any time without penalty. All EEG and behavioral data collected will be stored securely on institutional servers equipped with firewalls and advanced security protocols compliant with relevant data protection regulations. Hard copies will be securely locked and accessible only to designated research personnel. Data will be anonymized with unique identifiers to protect participant confidentiality. Analysis datasets will be fully de-identified. Secure long-term storage and data sharing practices will adhere strictly to institutional ethics guidelines and the oversight of the Ethics Committee of the School of Psychology, South China Normal University, which reviewed and approved the study protocol.

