The pattern of results will be evaluated against two complementary sets of predictions. If the theory-driven framework (EPF/WCC/NCH) is supported, we expect to see a dissociation: relatively intact or enhanced neural responses (e.g., MMN amplitude, factor scores) to single-feature deviants (e.g., consonant-only, vowel-only), but attenuated or delayed responses to multi-feature deviants (e.g., V + T, C + V + T). This pattern would align with models that posit a cognitive style in ASD characterized by heightened local sensitivity paired with impaired global integration. It would suggest that children with ASD can detect individual phonetic cues but struggle to bind them into unified, linguistically meaningful percepts. If the data-driven framework (MMN literature) is supported, we expect to see a graded, complexity-dependent deficit: reduced MMN amplitudes and prolonged latencies across all conditions, with the most severe effects in multi-feature and tone-involving contrasts. This would be consistent with the Neural Complexity Hypothesis and would suggest a more general processing burden in ASD, where increasing feature complexity leads to cumulative degradation in neural responsiveness, regardless of a local/global distinction. If the results reveal a mixed or unexpected pattern (e.g., no group difference in tone processing), this would highlight the heterogeneity within the ASD population and challenge the universality of current models. Such findings would prompt a re-evaluation of assumptions about what constitutes “local” or “global” processing and could point to subgroup-specific profiles (e.g., based on language ability or sensory preference) that are not captured by broad theoretical frameworks.

A key aspect of our analysis is the inclusion of hemispheric asymmetry as a data-driven prediction. While EPF, WCC, and NCH do not explicitly predict reduced left-hemispheric specialization, the MMN literature suggests that children with ASD may show less lateralized or right-shifted MMN responses to speech sounds. If this is confirmed, it would provide critical evidence for atypical neural organization in ASD, one that may underlie broader difficulties in processing rapid, temporally precise linguistic cues.

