## 6. Limitations and Future Directions

Several limitations should be acknowledged. First, as with many ERP studies involving clinical populations, sample sizes, particularly within the ASD group, may limit statistical power, especially for detecting nuanced interaction effects. Mitigation strategies include the use of permutation-based statistical corrections and robust within-subject analyses. Second, ERP morphological variability across participants may complicate t-PCA component matching, potentially affecting component stability and RDM construction consistency. Efforts are made to standardize preprocessing and component validation procedures. Third, theoretical RDMs employed in RSA may oversimplify the complex acoustic–phonetic realities of natural speech, potentially affecting ecological validity. Future work could refine these models to encompass finer-grained acoustic and linguistic parameters.

Furthermore, the complex interactions among phonological features (tone, vowel, consonant) may exceed the explanatory scope of current cognitive frameworks such as EPF and WCC. Our study is exploratory in nature, designed not to definitively test these broad theories in their entirety, but to derive and evaluate specific, constrained predictions about local versus global auditory encoding. Findings should therefore be interpreted as preliminary insights into neural processing differences, rather than conclusive evidence for or against any single theoretical account.

Additionally, while the multi-feature oddball paradigm enables precise manipulation of phonological features, it uses isolated syllables in a passive listening context, which lacks the temporal, syntactic, and semantic richness of natural communication. We acknowledge that this design does not fully capture real-world language processing and is not equipped to test high-level cognitive models (e.g., Bayesian Predictive Coding [87,88,89]) in their complete form. Instead, it provides a controlled, developmentally sensitive window into early auditory integration. Future research should extend these findings using connected speech, predictive paradigms, or naturalistic listening tasks [90,91].

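### Tables 1 and 2 give the equals sign no criterion, so a non-significant single-feature result would by default be read as intact and count toward the theory-driven account

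*Protocol article*

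**What the plan says.** The key under both prediction tables reads "Note: ↑ represents significant increase. ↓ represents significant decrease", and the equals sign "represents similar results when comparing MMN responses in ASD group with those in the TD group". No margin, interval or equivalence criterion is given for similarity.

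For consonant-only and vowel-only deviants, Table 1 predicts an upward arrow "or = MMN amplitude ↓ or = MMN latency", and its WCC + NCH column describes both as intact. Table 2 predicts lower amplitude for the consonant, equal or lower amplitude for the vowel, and longer latency for both.

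Section 5 states: "The pattern of results will be evaluated against two complementary sets of predictions". The theory-driven account is supported by "relatively intact or enhanced neural responses (e.g., MMN amplitude, factor scores) to single-feature deviants" combined with attenuated or delayed responses to multi-feature deviants. A third branch covers mixed or unexpected patterns.

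The Figure 2 caption gives t-tests and ANOVA as examples of the testing, used "to assess group differences or condition effects". Section 2.1.1 plans the study "at a significance level of α = 0.05", and Section 2.1.2 sets 30 children per group. Section 6 concedes that sample sizes "may limit statistical power, especially for detecting nuanced interaction effects".

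**The concern.** The arrows take up every significant result. The equals sign is the only symbol left and has no criterion of its own, so a non-significant result falls to it by default. In a study of this size, absence of significance is weak evidence that a response is intact. A child group with a real, moderate reduction in consonant discrimination could be described as having preserved local processing. If one or more multi-feature cells reach significance, the result could then be presented as the dissociation that distinguishes the theory-driven account from a general, graded deficit. The comparison between the two accounts is what the dual framework is for.

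**Working it through.** **1. Where the equals sign separates the accounts**

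| Cell | Table 1 | Table 2 | What a null favours |
|---|---|---|---|
| Consonant amplitude | ↑ or = | ↓ | theory-driven |
| Consonant latency | ↓ or = | ↑ | theory-driven |
| Vowel latency | ↓ or = | ↑ | theory-driven |
| Vowel amplitude | ↑ or = | = or ↓ | neither |

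Tone latency runs the other way (Table 1 ↑, Table 2 = or ↑): a null there would favour the data-driven account.

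**2. Inputs**

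- n = 30 per group (Section 2.1.2).
- α = 0.05 (Section 2.1.1). Sidedness is not stated; two-sided is assumed.
- No standard deviations are given, so standardised differences d are assumptions. The anchor is the protocol's own f = 0.25; for two groups d = 2f = 0.5.

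The stated minimum of 52 children does not reproduce from the stated inputs. With f entered as the effect size of the named MANOVA procedure, 128 are needed for two measurements and 226 for seven. Values near 52 appear only with inputs the article does not state. That is a separate matter and does not enter below, where the planned 30 per group is used.

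**3. Chance that a real reduction is non-significant in one condition**

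Two-sample t test, 58 df, critical value 2.002, non-centrality d × √(30/2) = 3.873d. At d = 0.5 the non-centrality is 1.936 and power is 0.478.

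| d | Power | Non-significant |
|---|---|---|
| 0.3 | 0.208 | 79% |
| 0.4 | 0.332 | 67% |
| 0.5 | 0.478 | 52% |
| 0.6 | 0.628 | 37% |
| 0.8 | 0.861 | 14% |

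**4. What a null leaves open**

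The 95% interval half-width is about 2.002 × √(2/30) = 0.52 SD. An estimate just short of significance is therefore compatible with a reduction of about 2 × 0.52 = 1.03 SD.

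**5. Chance of the complete false pattern**

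Section 5 also requires multi-feature attenuation, so a single-feature null is only half of it. Simulation for amplitude: 20,000 studies, 30 per group, seven conditions, correlation 0.5 between conditions (assumed), each tested at two-sided 5%. The uniform scenario has d = 0.5 everywhere. The graded scenario has d = 0.4 for single, 0.6 for dual and 0.8 for triple deviants (assumed). Neither scenario has intact single-feature responses.

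| Consonant and vowel both without significant decrease, and… | Uniform | Graded |
|---|---|---|
| (no further condition) | 35% | 52% |
| at least one multi-feature cell significantly reduced | 20% | 46% |
| at least three of the four | 4% | 22% |
| all four | 0.9% | 9% |

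Requiring tone to be significantly reduced as well lowers the last row to about 0.5% and 3%. Latency was not simulated.

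**The case against.** No sentence says that a non-significant result is scored as intact. The rule is inferred because no other symbol is available, and the notes are keys to tables of tentative predictions. This stands as a limit: it is a default reading, not a stated procedure. An analysis plan that is not shown could add a margin. But the symbols are defined in this article, one by significance and one without any criterion, and Section 5 interprets results against them.

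A reader might infer that any single-feature null confirms the theory-driven account. The documents do not support that. A vowel-amplitude null fits both tables, a significant delay in the same cells would contradict Table 1, and multi-feature attenuation is also required. Nor is the 35% chance of two single-feature nulls the chance of a false dissociation. Under strict matching a uniform deficit produces the full pattern in about 1% of studies, and many of the other results would belong in the mixed branch of Section 5.

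The study also calls itself exploratory and its framework provisional, and it concedes limited power. That lowers the stakes. It does not say how a null is kept apart from similarity, and the close of Section 3.2.2 still presents the framework as a test between competing accounts with falsifiable outcomes.

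**Conclusion.** The concern holds as a flaw in how null results would be read. As the notes stand, a non-significant consonant amplitude, consonant latency or vowel latency would by default count toward the theory-driven account and against its rival. At a true d = 0.5 such a null is slightly more likely than not (52%). The resulting false dissociation ranges from about 1% to 20% under a uniform deficit and from about 9% to 46% under the graded one. The spread reflects the fact that the article does not say how many multi-feature cells must match. These figures rest on assumed effect sizes, a two-sided test without multiplicity adjustment, and a between-condition correlation of 0.5. It is worth correcting before the results are interpreted. It does not invalidate the design.

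**What to change.** In both table notes, state that a non-significant difference is not an equals sign. It is reported as inconclusive and counts for neither framework, unless the confidence interval for the ASD–TD difference excludes a reduction (or delay) larger than a margin that the investigators choose and state in advance.

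In Section 5, require the dissociation to rest on two things together:

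- a significant group-by-condition contrast of single- against multi-feature deviants, stating on which side tone falls. This agrees with the within-between interaction used for sample size in Section 2.1.1;
- the interval above for the single-feature conditions. The contrast alone is not enough, because a deficit that grows with complexity also produces it.

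The cost is the wording of two notes and a sentence or two in Section 5, with no new data. The downside is that many single-feature cells will be inconclusive. As an illustration only, take a margin of 0.5 SD and no true difference. A 90% interval (critical value 1.672) would exclude a larger reduction with probability about Φ(1.936 − 1.672) = Φ(0.26), or 60%. Requiring it to exclude differences of that size in both directions succeeds about 21% of the time. A wider margin is easier to meet but says less about intactness.

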## Data Availability

The data presented in this study are available on request from the corresponding author due to IRB requirements for data management and regulation.
